#### CAU

According to the Dutch Multidisciplinary guidelines for the diagnosis and treatment of ADHD [76], CAU for children aged 8–16 years consists of psycho-education and the prescription of medication approved for ADHD and/or evidence-based parent and/or teacher-administered behaviour therapy, preferably both medication and behaviour therapy. First-line option for medication is a psychostimulant, second-line options are atomoxetine or alpha-2 presynaptic agonists. Participants in the CAU-group will be informed that it is not allowed to participate in a mindfulness programme until the 2-month follow-up assessments of the study.

#### Expectancy, satisfaction, compliance and healthcare consumption

For family MBI and CAU condition, credibility and expectancy of clinical outcome will be evaluated with the parent-rated 6-item Credibility/Expectancy Questionnaire (CEQ, translation to Dutch by the authors for this study) [77]. The CEQ shows a good internal consistency and test-retest reliability [77]. Satisfaction with family MBI/CAU will be assessed in parents and children at end of treatment, 2- and 6-month follow-up. Parental and child compliance with the mindfulness practices, and child adherence with any ADHD medication, will be assessed in the parents at the same three time points. Type and dose of possible ADHD-medication and other medication will be assessed at all time points for parent and child. At baseline parents will report which treatments for ADHD the child received prior to study participation. In addition, child healthcare consumption between assessments will be assessed with a 30-item adapted version of the parent-rated Trimbos and iMTA questionnaire on Costs associated with Psychiatric illness (TiC-P) [78] at end of treatment and both follow-up time points. Parental healthcare consumption during the whole study period will be assessed with the 46-item self-rated TiC-P at 6-month follow-up. The TiC-P is a valid questionnaire with a sufficient to high test-retest validity (ICC > .6) [79].

### Assessments

#### Descriptives

Clinical ADHD diagnosis will be confirmed using a structured psychiatric interview (Schedule for Affective Disorders and Schizophrenia for School-Age Children-Present and Lifetime Version; K-SADS-PL) [80], adapted to DSM-5 and administered to a parent by a trained researcher. The focus of the interview will be on the behaviour of the child off medication in the past half year. Further, parents will be screened for the presence of adult psychiatric disorders, using the 10-item Kessler Psychological Distress Scale (K10) [81]. For those with elevated scores (25 or higher) a diagnostic interview (Mini-International Neuropsychiatric Interview; MINI) [82] will be administered to establish axis-I disorders by a trained researcher. In case no valid IQ test results of participants are available, full-scale IQ will be estimated by two subtests of the Wechsler Intelligence Scale for Children-Third Edition (WISC-III) [83] or Wechsler Adult Intelligence Scale-Third Edition (WAIS-III) [84]: Vocabulary and Block Design. These subtests together are known to correlate between .88–.91 with the Full-scale IQ [85, 86]. Standardised questionnaires completed by parents as part of routine intake procedures at Karakter will give us a wide range of additional background information on variables such as age, gender, medical/medication history, ethnicity, family-structure and socioeconomic status. Some additional participant characteristics will be collected at baseline as there might be changes in family-structure or socioeconomic status between intake at Karakter and study participation. The Pubertal/Physical Development Scale (PDS) [87] will be used to assess the pubertal developmental stage of the child at baseline and 6-month follow-up.

#### Primary outcome measure

##### Parent-rated child self-control

To measure self-control of the child, we will use the parent-rated version of the BRIEF [88], which assesses real-life self-control skills across situations and is used in clinical and research settings for ADHD. The questionnaire consists of 75 items with a 3-point rating scale ranging from 1 (*never*) to 3 (*often*) with higher scores indicating more problems in executive functioning. The BRIEF gives rise to a global executive composite score as well as two broad indexes (Behavioural Regulation and Metacognition) and eight subscales (Inhibit, Shift, Emotional Control, Initiate, Working Memory, Plan/Organise, Organisation of Materials, and Monitor). The internal consistency of the Dutch version is sufficient when administered to adolescents with ADHD (Cronbach’s α coefficients ranging from .69 to .95) [55]. Test-retest reliability is high with intra-class correlations of ≥.73. The BRIEF demonstrates good convergent validity [88].

#### Secondary outcome measures for children

##### Teacher-rated child self-control

Child self-control will also be assessed using teacher-ratings on the BRIEF-T [88]. Teachers have the advantage to be able to evaluate the child’s behaviour in the context of their peers’ behaviour and of the normative range, and are blinded to exactly which intervention is provided to the child at home and/or in the clinic [89]. The BRIEF-T consists of 75 items with the same 3-point rating scale and structure as the parent form. The Dutch version shows a good internal consistency, with Cronbach’s α coefficients ranging from .88 to .98, and a high test-retest reliability (ICC = .77 for the global executive composite score) [88].

##### Computerised tasks of child self-control

Logan’s Stop Signal task will be used to measure motor inhibition [90, 91]. In this task, participants are presented with go-trials which consist of the presentation of a stimulus (i.e. either the letter O or the letter X) and are instructed to press the corresponding response button as quickly and accurately as possible. In 25% of the trials, at random, the go-trial is followed by an auditory stop-signal (i.e. a tone). In those trials, participants are required to withhold their response. The delay between the go and the stop signal is varied using a dynamic tracking algorithm, such that an average person has a 50% chance of correctly withholding their response at a stop-trial. The two main dependent behavioural measures will be the percentage of errors and the Stop Signal Reaction Time (SSRT), which is calculated by subtracting the Mean Delay from the Mean Correct Reaction Time [90]. Secondary behavioural outcome measures will be reaction time variability and speed accuracy trade off [92]. The Stop Signal task shows an adequate test-retest reliability when administered to children with ADHD (ICC = .72 for the SSRT) [91].

Temporal discounting refers to the decrease of subjective reward value as a function of increasing delay [93]. In the Temporal Discounting task that will be used in this study [94, 95] participants are asked to choose between a smaller immediate reward (i.e. one, two, three of four eurocents) and a larger delayed reward (i.e. five eurocents) during forty trials. Choices are visually represented by two airplanes on a computer screen. Delays are represented by the “height” at which the planes are flying, and vary between five and sixty seconds. Participants choose the preferred plane which results in earning the chosen amount, immediately or after the appropriate delay. A maximum of two euros can be earned. The computer task will be followed by a debriefing on the child’s choices and emotions regarding every delay interval using the Self-Assessment Manikin. This measure is shown to be a reliable, non-verbal method for assessing a person’s emotional reaction in response to a certain event or stimulus [96]. Outcome measure will be the subjective reward value, defined as the magnitude of the smaller immediate reward that leads to indifference of the participant towards the larger delayed reward [93]. At this point, the participant shows no clear preference for one of the rewards, either the delayed or the immediate one. The real Temporal Discounting task (with actual money and delays) has a clear advantage compared to hypothetical tasks in terms of ecological validity [97] and is proven useful in assessing individual differences in children versus adolescents [94] and individuals with less and more hyperactivity/impulsivity symptoms [98].

The Probabilistic Reversal Learning task will be used to determine the cognitive ability to adapt behaviour according to changes in stimulus-reward contingencies, also known as cognitive flexibility [99]. An experimental study has shown impaired reversal learning to reflect reduced inhibitory control of affective responses, and therefore might be related to deficits in self-control [100]. In the Probabilistic Reversal Learning task participants repeatedly choose between two visual stimuli during eighty trials, followed by rewarding or punishing auditory feedback. In 80% of the trials, the choice is followed by actual feedback (i.e. rewarding tone with correct response and punishing tone with incorrect response) and in 20% by misleading feedback. The stimulus-outcome contingencies reverse unannounced after forty trials, resulting in the previous mostly rewarded stimulus now being mostly punished and vice versa. Subjects are instructed that the contingencies may change, but do not know when or how often. Thus, the difficulty in performing the task comes from the need to integrate feedback over a number of trials because negative feedback may either be a probabilistic punishment or signal a true reversal. Outcome measures will be Ratio Win-Stay (the number of times the participant repeats their choice following a rewarded trial, divided by the total times the participant repeats their choice), Ratio Lose-Shift (the number of times the participant shifts response following a punished trial, divided by the total times the participant shifts choices) and perseverative errors (two or more consecutive error responses during the reversal phase) [99]. The Probabilistic Reversal Learning task is a well-defined and ecological instrument which is widely used measuring cognitive flexibility in children [101] and adolescents [102]. Neurocognitive test instructions to children can be found in Additional file 1.

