##### Computerised tasks of parental self-control

The parents’ version of the Stop Signal task and the Probabilistic Reversal Learning task will be identical to those described for children. The Stop Signal task shows an adequate test-retest reliability when administered to adults without a DSM-IV diagnosis in the past year (*r* = .65 for the SSRT) [115]. The Probabilistic Reversal Learning task shows adequate results when administered to adults with schizophrenia (ICC ranging from .49 to .68) [116].

As the Temporal Discounting task that will be used for children is not appropriate for use in adults, a hypothetical Temporal Discounting task will be administered to the parents. Participants make a series of choices regarding fictional amounts of money (rewards), ranging between one and hundred euros, available now versus after a specified delay interval (i.e. one month, one year, five years, ten years). Instructions are presented on the screen and are identical to those used by R. M. Hurst, H. O. Kepley, M. K. McCalla and M. K. Livermore [117]. For each trial, two variable rewards are presented in a random order, to increase the likelihood that the decisions are based on the amount in the individual trial and not on the previous trial. The participant’s score on the different delay intervals is the reward value where they switch between taking the delayed reward to taking the immediate one. The hypothetically Temporal Discounting task is widely used in various studies [97] and shows good internal consistency (α = .89) when administered to adults with and without self-reported ADHD [117]. Neurocognitive test instructions to parents can be found in Additional file 1.

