### Statistical analyses

Data will be analysed and reported according to CONSORT guidelines. Baseline demographic and clinical characteristics of the family MBI- and CAU-groups will be compared to examine whether these have been distributed evenly across the two groups by the randomisation. The primary analyses will be aimed at comparing results on the outcome measures at end of treatment between the family MBI and CAU condition, controlling for baseline levels and possible other baseline differences between intervention and CAU groups. To test our primary hypothesis that assignment to family MBI (relative to CAU) will improve child self-control, we will use ANCOVA with group condition (family MBI versus CAU) as the primary independent variable, and child self-control (continuous BRIEF-P score) at end of treatment as the primary dependent variable and child self-control at baseline as covariate. Cohen’s d effect sizes will be calculated. Analyses will be conducted both according to intention-to-treat principle, and per-protocol on completers (family MBI condition: child and parent attended > = 4 family MBI sessions). Intention-to-treat analyses will be conducted using available case analysis (not considering individuals with missing data) as well as imputation, as described in [145]. In case both parents participate in the assessments, data of the parent with the most complete dataset will be used for the ANCOVA, and if both are complete, the sex of the parent (or age, for same-sex parents) will determine which dataset will be used so that the fathers:mothers ratio is most similar across both study arms.

Secondary analyses, aimed at examining the consolidation of treatment effects at follow-ups, will use multilevel modelling with time point as repeated measurement, following the approach described in [58]. Moreover, we will conduct a set of complementary analyses to derive prediction models for response to intervention from baseline characteristics, and explore interactions between child and parental outcomes.

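### Stop-signal reaction time is scored as mean go RT minus mean delay, which adds the right skew of the go responses to the inhibition score

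*Protocol article*

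**What the plan says.** Under *Computerised tasks of child self-control*, the protocol article describes a stop-signal task in which a quarter of trials carry a stop tone. The delay is "varied using a dynamic tracking algorithm, such that an average person has a 50% chance of correctly withholding their response at a stop-trial". SSRT is one of the task's two main measures, next to the percentage of errors, and is fixed as a formula "which is calculated by subtracting the Mean Delay from the Mean Correct Reaction Time". The same paragraph adds: "Secondary behavioural outcome measures will be reaction time variability and speed accuracy trade off".

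The section *Computerised tasks of parental self-control* states that the adult "version of the Stop Signal task and the Probabilistic Reversal Learning task will be identical to those described for children", so the same score applies to parents. *Statistical analyses* sets out the main comparison as "comparing results on the outcome measures at end of treatment between the family MBI and CAU condition, controlling for baseline levels".

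The article does not give the number of trials, the step of the tracking algorithm, the RT distribution, a trimming rule or the handling of omitted go responses. Such detail may stand in a fuller document. The scoring formula itself is stated here and is not left open.

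**The concern.** Tracking to 50% ties the delay to the middle of the go RT distribution, that is, to the median. Subtracting that delay from the mean leaves the mean-median gap inside the inhibition score. For right-skewed RTs the gap is positive and grows with the slow tail. Tracking at 50% does not protect the formula, because it is what creates the mismatch.

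This matters here because the intervention is partly an attention training: the Background names better attention control as one of its mechanisms. If it shortened the slow tail and left stopping speed alone, the planned SSRT would fall. That fall could be read as better motor inhibition, and SSRT and RT variability would partly report the same change.

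**Working it through.** **Inputs from the protocol article:** the formula, tracking to 50% stopping, and 25% stop trials. **Assumed, because the article does not give them:** ex-Gaussian go RTs (normal part with mean μ and SD σ, plus an exponential tail τ), a true SSRT of 250 ms, the number of trials and the tracking step.

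**1. Algebra.** A response escapes on a stop trial when go RT < delay + SSRT. Tracking settles where this has probability 0.5:

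- delay + SSRT = median RT, so delay = median RT − SSRT.
- Planned score = mean RT − delay = SSRT + (mean RT − median RT).

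**2. The 50% figure.** With long tracking (2000 stop trials, 10 ms steps), the simulated proportion of failed stops is 0.497 to 0.500, so the stated target is reproduced. With 64 stop trials it is 0.458 to 0.501, because the staircase needs time to settle.

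**3. Check of the algebra** (μ 450, σ 60, 2000 stop trials, 10 ms steps, true SSRT 250 ms):

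| τ (ms) | mean − median RT | planned score | excess over 250 | integration |
|---|---|---|---|---|
| 50 | 5.1 | 254.9 | 4.9 | 249.8 |
| 100 | 18.9 | 268.0 | 18.0 | 248.8 |
| 150 | 35.5 | 284.0 | 34.0 | 247.8 |
| 200 | 52.7 | 301.7 | 51.7 | 248.1 |

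The excess follows the mean-median gap.

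**4. A session of more realistic length** (192 go and 64 stop trials, μ 450, σ 80, 50 ms steps, SSRT 250 ms with SD 40, no trimming):

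| τ (ms) | planned score | excess over 250 | integration |
|---|---|---|---|
| 60 | 253.9 | 3.9 | 248.2 |
| 100 | 262.7 | 12.7 | 246.2 |
| 150 | 278.2 | 28.2 | 243.5 |
| 200 | 295.8 | 45.8 | 241.5 |

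From τ = 150 to τ = 100 the planned score falls by 278.2 − 262.7 = 15.5 ms with stopping unchanged. Integration moves by 246.2 − 243.5 = 2.7 ms the other way.

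**5. Trimming.** With the same settings, but go RTs above 1000 ms dropped, the planned score is 261.4 ms at τ = 150 and 260.2 ms at τ = 100. The difference is 1.2 ms. An upward bias of about 10 ms remains but is nearly equal at the two tails.

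**6. Symmetric spread.** With no tail and long tracking, the planned score is 250.5 ms at SD 60 and 251.4 ms at SD 150. In short sessions (64 stop trials, 50 ms steps) it is 253.2 and 256.0 ms. A score built on the median gives 253.3 and 256.1 ms there, so that small rise comes from staircase start-up and not from skew.

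**7. Group comparison** (42 per arm, baseline-adjusted ANCOVA, true SSRT unchanged in both arms, mean baseline τ 200, untrimmed):

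| τ in the intervention arm | μ held: effect, rejections | mean RT held: effect, rejections |
|---|---|---|
| 200 (unchanged) | −0.5 ms, 5.2% | −0.4 ms, 5.6% |
| 150 | −18.1 ms, 61% | −15.0 ms, 46% |

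The simulation keeps each child's true SSRT identical at both visits and shortens every tail in the intervention arm by the same fraction. The rejection rates therefore illustrate the mechanism and do not forecast the trial.

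**8. Omitted go responses** (τ = 150, 10% omissions assumed). The planned formula gives about 254 ms. Integration on observed RTs alone gives about 218 ms, which is worse. Integration with omitted trials kept in as the slowest RT stays at about 237 to 248 ms across all tail, trimming and omission settings tried.

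**The case against.** The strongest case against the point runs as follows.

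- **Size.** Every millisecond figure rests on an assumed distribution, and the 15 ms shift also assumes that the intervention cuts the tail by a third. A trimming rule, which an article may leave to a fuller document, can nearly remove the shift. This stands: no size can be claimed for this trial.
- **Variability.** A reader might infer that any drop in RT variability will pass for better inhibition. Step 6 does not support that. Only right skew drives the bias.
- **Comparison between arms.** A reader might infer that the planned comparison is itself biased. The documents do not support that either. With skew unchanged in both arms, rejections stay at about 5%. Harm needs an effect on the slow tail in one arm, and the article's evidence on attention is mixed: weak for attentional control in the adult meta-analysis, but with an effect of d = .41 on executive attention in a family-based trial in young children with ADHD.
- **Visibility.** RT variability is also reported, so a parallel fall would be seen. True, but seeing it would not show how much of the SSRT change it explains.
- **Established formula.** The definition is cited, and the article gives an ICC of .72 for SSRT in children with ADHD. Comparability is a fair reason to keep the planned score as a second result. Test-retest reliability does not speak to this bias, since a stable skew is itself repeatable.
- **The alternative has faults.** Integration runs low with coarse steps and long tails, and badly low if omitted responses are ignored. This stands and shapes the fix.

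**Conclusion.** The point holds as a modest one about a secondary outcome in children and parents. The stated formula adds the mean-median gap of the go RTs to SSRT. This follows from 50% tracking under the race model, without any outside figure.

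Its size is not known from the document. Under ex-Gaussian RTs with tails of 60 to 200 ms and no trimming, the bias is about 4 to 46 ms. A tail of 150 against 100 ms gives a difference of about 15 ms untrimmed and about 1 ms if go RTs above 1000 ms are dropped. A false reading of better inhibition arises only if the slow tail changes differently between arms, which is plausible for an attention training but not shown.

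The parent-rated BRIEF, its ANCOVA and the sample size are not affected.

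**What to change.** Fix the scoring before the arms are compared, for children and parents alike:

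- Score SSRT by the integration method: the go RT at the quantile equal to the participant's own proportion of failed stops, minus the mean delay.
- Keep all go trials in the distribution, give omitted go trials the slowest RT, and do not trim slow responses out. Since the quantile lies near the middle, the exact slow value given to omissions hardly matters.
- Report the planned mean-based score as a sensitivity result.

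No new data are needed. The cost is a change in the scoring script, a sentence or two in the analysis plan, and less direct comparability with earlier studies that used the mean-based score and with the cited ICC. The sensitivity result limits that loss.

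### Ratio Win-Stay and Ratio Lose-Shift are divided by total stays and total shifts, so neither isolates the response to reward or to punishment that its name implies

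*Protocol article*

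**What the plan says.** The protocol's section on computerised tasks of child self-control introduces the Probabilistic Reversal Learning task to "determine the cognitive ability to adapt behaviour according to changes in stimulus-reward contingencies, also known as cognitive flexibility". The design is simple: "participants repeatedly choose between two visual stimuli during eighty trials"; "In 80% of the trials, the choice is followed by actual feedback", with misleading feedback on the remaining 20%; and "The stimulus-outcome contingencies reverse unannounced after forty trials".

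Three outcomes are named, with reference [99] given as the source. Two of them are ratios:

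- The win-stay ratio is given as "the number of times the participant repeats their choice following a rewarded trial, divided by the total times the participant repeats their choice". Its denominator is therefore every stay, whatever feedback came before it.
- For the lose-shift ratio the text has "the number of times the participant shifts response following a punished trial, divided by the total times the participant shifts choices". Here every shift counts in the denominator, again regardless of the preceding feedback.

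The third outcome, perseverative errors, uses neither denominator. The section on parental tasks carries the definitions over: "The parents’ version of the Stop Signal task and the Probabilistic Reversal Learning task will be identical to those described for children". No other section gives a different denominator. All of these are secondary outcomes.

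**The concern.** A win-stay measure is meant to say how often a participant stays when the last choice was rewarded. A lose-shift measure is meant to say how often a participant shifts when the last choice was punished. Both condition on the feedback. The stated definitions condition on the response: they give P(win | stay) and P(loss | shift), where the names and the stated purpose call for P(stay | win) and P(shift | loss).

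A difference between arms on the stated Win-Stay could therefore arise when both arms treat reward identically and differ only after punishment. A real difference in shifting after punishment could equally go unseen in the stated Lose-Shift. This concerns two of the three outcomes of this task, in children and in parents.

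**Working it through.** The protocol gives no numerical result for these indices, so there is no figure to reproduce. The check is algebra plus a simulation of the task.

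**Inputs from the protocol.** 80 trials, reversal after trial 40, 80% valid and 20% misleading feedback, and the two definitions above.

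**Assumptions.** Each simulated participant has a fixed s = P(stay | win) and h = P(shift | loss). The documents give no such values, so a range is shown. There were 20,000 runs per profile. The last trial has no following response and is not scored.

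**Formulas.** With w the proportion of rewarded trials:

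- stated Win-Stay = s·w / [s·w + (1−h)(1−w)]
- stated Lose-Shift = h(1−w) / [h(1−w) + (1−s)·w]

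Each contains w and both tendencies. With the number of rewarded or punished trials as denominator, the ratios estimate s and h directly.

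**1. Same response to reward, different stated Win-Stay.**

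- s = .95, h = .10, simulated w = .546: (.95×.546) / (.95×.546 + .90×.454) = .519 / .927 = .56.
- s = .95, h = .60, simulated w = .643: (.95×.643) / (.95×.643 + .40×.357) = .611 / .754 = .81.

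The simulated means agree (.56 and .81). The feedback-based Win-Stay is .95 for both.

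**2. Different response to punishment, same stated Lose-Shift.** If s = 1, the term (1−s)·w is zero and the stated Lose-Shift equals h(1−w) / h(1−w) = 1 for every h above zero. The simulation confirms 1.00 at h = .05, .10, .50, .90 and 1.0. Over h = .10, .50 and .90 it is the stated Win-Stay that moves, from .64 to .80 to .95, although s is unchanged.

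**3. The order can reverse.**

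- s = .60, h = .90, simulated w = .567: (.60×.567) / (.60×.567 + .10×.433) = .340 / .384 = .89.
- s = .95, h = .20, simulated w = .591: (.95×.591) / (.95×.591 + .80×.409) = .561 / .889 = .63.

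The participant who stays less often after reward has the higher stated Win-Stay.

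**4. Feedback ignored.** If 1−h = s, the formula reduces to w, which was about .50 for every such profile simulated, so the stated Win-Stay is about .50 whatever the overall stay rate.

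| s | h | stated Win-Stay | feedback-based Win-Stay | stated Lose-Shift | feedback-based Lose-Shift |
|---|---|---|---|---|---|
| .95 | .10 | .56 | .95 | .63 | .10 |
| .95 | .60 | .81 | .95 | .87 | .60 |
| 1.0 | .10 | .64 | 1.00 | 1.00 | .10 |
| 1.0 | .90 | .95 | 1.00 | 1.00 | .90 |
| .90 | .10 | .50 | .90 | .50 | .10 |
| .50 | .50 | .50 | .50 | .50 | .50 |

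**5. Undefined scores.** A participant who never shifts has a stated Lose-Shift of 0/0. This occurred in about 46% of runs at a 1% shift rate and in about 2% at s = 1.0, h = .10, and in essentially none of the more responsive profiles.

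**The case against.** **The source.** The definitions are attributed to reference [99], which is not at hand. If it uses these ratios, the protocol follows a published index and a change would cost comparability. If it uses feedback-based denominators, the text is a slip in a condensed article and the scoring code may already be conventional. The documents cannot settle which. This stands and belongs in the fix. In either case the ratios as printed do not isolate the tendencies they are named for.

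**The ratios are not empty.** A reader might infer that they do not measure response to feedback at all. That goes too far. In a separate simulation of 5,000 reinforcement learners (assumed learning rates .05 to .95 and choice sensitivities .3 to 5), the stated Win-Stay and Lose-Shift had rank correlations with choice accuracy of .63 and .53. The feedback-based versions had .71 and −.49. The stated Lose-Shift, however, correlated −.25 with the true lose-shift tendency, so its label describes it poorly.

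**The always-stay participant.** The stated Win-Stay gives .50 both to someone who always stays and to someone who responds at random. This is not plainly an error, because both ignore feedback. The feedback-based Win-Stay gives the always-stay participant a perfect 1.0, although that participant is wholly inflexible. The point is fair, and it is why the two feedback-based ratios should be read together: the same participant has a Lose-Shift of 0.

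**Rare extremes.** Undefined scores need no shift at all, from participants told that contingencies may change. With win-stay drawn from .5 to 1 and lose-shift from .05 to .9, they occurred in .02% of runs. They are a minor matter outside near-perseverative behaviour.

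**Small reach.** These are two indices of one of three computerised tasks, and the protocol itself prefers questionnaire ratings to neurocognitive tests. This is accepted.

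**Conclusion.** The definitions are wrong as written for what the indices are called and for the task's stated purpose. The stated ratios carry some signal about the use of feedback, but it is confounded by reward rate, overall tendency to stay and the response to the opposite feedback. An equal true win-stay of .95 can score .56 or .81, and the stated Lose-Shift cannot tell .05 from 1.0 when win-stay is 1.0. The algebra follows from the definitions. The sizes rest on assumed behavioural profiles, and nothing in the documents shows how common such profiles are or whether they would differ by arm.

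A reader might go on to infer that the trial's conclusions on cognitive flexibility would be wrong. The documents do not support that: perseverative errors are unaffected, and an arm difference in the confounding behaviour is possible but not shown. The effect is confined to two secondary indices, in children and in parents. The primary BRIEF-P analysis and the sample size are untouched.

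**What to change.** Redefine the two indices, for children and parents:

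- Ratio Win-Stay = stays after rewarded trials / number of rewarded trials.
- Ratio Lose-Shift = shifts after punished trials / number of punished trials.

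Exclude the last trial from numerators and denominators. Report the two ratios side by side, so that a high Win-Stay from never shifting is recognised as such.

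Before scoring, compare the scoring code and reference [99] with the text. If the code already uses feedback-based denominators, only the text needs correcting. If [99] uses the stated ratios, they may be kept as supplementary indices under a correct label: the proportion of stays that followed reward and the proportion of shifts that followed punishment.

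The cost is a change to two definitions and the matching scoring lines, made before analysis. No new data should be needed: the Monitoring section describes checks of data at item or trial level for the first participants, which suggests, without stating it, that trial-level records are kept. The one possible loss is comparability with [99], which the supplementary indices would cover.
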